### CINV susceptibility questionnaire

This questionnaire has been developed for use in this trial to determine participants’ predisposition to CINV. Previous research has reported several factors correlated with susceptibility to CINV. These include lifestyle factors (e.g. alcohol intake); previous experience of nausea and/or vomiting from causes other than chemotherapy (e.g. motion sickness, pregnancy); and participant characteristics (e.g. age, gender). It is estimated that the questionnaire takes approximately 5 minutes to complete.

### Edmonton Symptom Assessment System (ESAS)

The ESAS is a validated and reliable tool used to assess the severity of common symptoms experienced by cancer patients including pain, anxiety and drowsiness. It includes 10 items that are self-assessed by the patient using individual 10-point scales. This tool has been validated in this population and has reported a Cronbach’s α of 0.79 [45]. The tool will be administrated at -1 day and at 4 days post-chemotherapy for each cycle in order to determine treatment related side-effects. The tool should take approximately 5 minutes to complete.

### Patient Generated - Subjective Global Assessment (PG-SGA)

Nutritional status will be measured using the valid and reliable scored PG-SGA [46]. Using the data gained from this tool, statistical analysis will be conducted to determine the impact of CINV on the participants’ nutritional status. The PG-SGA will be conducted by a dietitian who has undergone training and testing for inter-rater reliability on nutritional status measures. The PG-SGA is specifically designed to assess the nutritional status of cancer patients. This tool provides a global rating of either A (well nourished), B (suspected or moderately malnourished) or C (severely malnourished). This global rating is based upon weight change, dietary intake, GI symptoms, a physical examination and the patient’s functional capacity. A total PG-SGA score is also calculated. A higher score reflects a higher risk of malnutrition and an increased need for nutrition intervention and symptom management.

### Functional Assessment of Cancer Therapy- General (FACT-G) and Fatigue (FACIT-F) subscale

The participants’ self-assessed QoL will be measured using the FACT-G questionnaire, a validated tool that has been widely used in this setting [47]. It contains 27 questions with a 5-point scale, which assesses four domains of patient QoL: physical well-being, social/family well-being, emotional wellbeing, and functional well-being. Strong concurrent validity with the Functional Living Index-Cancer tool was demonstrated with a Pearson coefficient of 0.79 [47]. Additionally, we have included the Functional Assessment of Chronic Illness Therapy- Fatigue (FACIT-F) subscale, a 13 item Likert scale, to assess self-reported symptoms of fatigue before and after each chemotherapy cycle. It is estimated to take between 5-10 minutes to complete.

### Adherence questionnaire

To assess the level of adherence to the study protocol, a questionnaire was developed for patients to record if and when they consumed the ginger/placebo doses per day. This is achieved by either recording the time or marking an X, depending on whether they consumed each dose, in the box corresponding to the dose in question. This is to be completed each day and is expected to take less than 2 minutes to complete.

### Timeline

The details of the study procedure are detailed below in chronological order. This timeline contains the details of the study process per cycle and will be repeated for 3 cycles (Figure 1).

**Figure 1 F1:**
[figure not shown]
Study flow diagram.

### Pre chemotherapy – 7 days prior to chemotherapy

The researcher will see patients as close as possible to 7 days prior to chemotherapy to determine their eligibility. If the patient is a viable candidate, informed consent will be obtained, the details of the study will be explained, and the supplements and questionnaire booklet will be delivered. Participants will be provided with written information and educated regarding the consumption of the supplement.

Participants will be randomised and provided with a 5 day (4 × 300 mg capsules per day) supply of ginger extract (20 capsules) or the placebo control (20 capsules) to be consumed daily with liquid in addition to their usual diet for 4 days, starting on the day of chemotherapy. The supplement will be provided in a sealed plastic container that will be packed by a researcher not involved in data collection.

Participants will be given a booklet containing the self-report questionnaires for CINV, QoL, adverse events, and blinding for the full study period per chemotherapy cycle (5 days). Each booklet will contain:

• One INVR questionnaire per day: one on the day of chemotherapy, and one each of the 4 days post-chemotherapy.

• Two FACT-G/FACIT-F questionnaires per cycle.

• One FLIE-5DR questionnaire per cycle.

• Two ESAS questionnaire.

• One CINV susceptibility questionnaire.

• One Adherence Questionnaire for each day the participant receives the study medication: one on the day of chemotherapy, and one for each of the 4 days post-chemotherapy.

• Instructions on how and when to complete these questionnaires will be included, as well the contact details of the study investigators.

During this consultation, the participant’s nutritional status will also be assessed using the PG-SGA assessment tool.

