**Methods/Design:**

In a double–blinded randomised-controlled trial, chemotherapy-naïve patients will be randomly allocated to receive either 1.2 g of a standardised ginger extract or placebo per day. The study medication will be administrated as an adjuvant treatment to standard anti-emetic therapy and will be divided into four capsules per day, to be consumed approximately every 4 hours (300 mg per capsule administered q.i.d) for five days during the first three cycles of chemotherapy. Acute, delayed, and anticipatory symptoms of nausea and vomiting will be assessed over this time frame using a valid and reliable questionnaire, with nausea symptoms being the primary outcome. Quality of life, nutritional status, adverse effects, patient adherence, cancer-related fatigue, and CINV-specific prognostic factors will also be assessed.

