### Hypothesis

It is hypothesised that in chemotherapy-naïve medical oncology patients about to commence treatment of any emetogenicity, adjuvant ginger supplementation compared with placebo will:

1. Reduce the frequency, distress and duration of chemotherapy-induced nausea (i.e. acute, delayed and anticipatory) during each chemotherapy cycle (up to 3 cycles).

2. Reduce frequency, distress and duration of chemotherapy-induced vomiting and retching

3. Result in improved nutritional status, physical function and quality of life

4. Be adhered to (>80% consumption of supplements) and well tolerated (no significant adverse events related to ginger supplementation).

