### Investigational plan

#### Overall study design

This study will be a double-blinded, randomised, placebo-controlled trial. Outcomes will be assessed at three days prior to chemotherapy, one day prior to chemotherapy, on the day of chemotherapy, and during the 4 days post-chemotherapy. Participants will consume the study medication for 5 days per chemotherapy cycle, commencing on the day of chemotherapy. This will be repeated over 3 chemotherapy cycles.

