### Study treatment

#### Ginger extract

The experimental treatment will be a commercial ginger extract manufactured by Bluebonnet Nutrition [41]. This preparation is in capsule form, and is standardised to contain 5% gingerols. Each capsule contains 300 mg of ginger extract with 15 mg of active ingredient per capsule (60 mg per 1.2 g) within white gelatine capsules.

A regimen of 4 capsules per day will be selected in order to incorporate the pharmacokinetics of ginger [36,37].

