### Day of chemotherapy

The following tools will be completed by the participant on the day of chemotherapy:

• One INVR questionnaire will be completed before chemotherapy commences.

• One CINV susceptibility questionnaire will be completed any time after chemotherapy has commenced.

• One adherence questionnaire.

Additionally, the participant is to consume one ginger/placebo capsule 1 hour before the administration of chemotherapy and then once every 4 hours after that for the remaining 3 capsules. The timing will be discussed with the participant to help ensure the participant understands the regimen.

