### Post-chemotherapy – day 4 post-chemotherapy only

At the end of day 4, participants will be asked to complete:

• One FACT-G/FACIT-F questionnaire

• One FLIE-5DR questionnaire

• One ESAS questionnaire

• One adherence questionnaire

Supplements are consumed using the same schedule as above.

At the end of day 4, participants will no longer be required to consume the oral supplements and any unconsumed supplements, along with the questionnaire booklet, will either be collected by the research team, along with the participant questionnaire booklet, during the participant’s next visit to the hospital or sent directly to the researchers using a reply-paid envelope. Unconsumed supplements of each individual will be counted in order to determine their level of adherence to the study protocol.

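### The dispensing text has a 5-day, 20-capsule supply taken for 4 days from the day of chemotherapy, against 5 dosing days everywhere else in the protocol

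*Protocol article*

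**What the plan says.** All references are to the protocol article.

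- Section on 7 days prior to chemotherapy: each participant is "provided with a 5 day (4 × 300 mg capsules per day) supply of ginger extract (20 capsules) or the placebo control (20 capsules" and the same sentence continues "to be consumed daily with liquid in addition to their usual diet for 4 days, starting on the day of chemotherapy".
- The same section's booklet list has one adherence form per medication day: one for the day of chemotherapy and one for each of the four days after it.
- Overall study design: "Participants will consume the study medication for 5 days per chemotherapy cycle, commencing on the day of chemotherapy".
- Abstract, Methods/Design: dosing is "for five days during the first three cycles of chemotherapy".
- Day of chemotherapy: "one ginger/placebo capsule 1 hour before the administration of chemotherapy and then once every 4 hours after that for the remaining 3 capsules".
- Post-chemotherapy, days 1-4: 4 capsules on each day.
- Post-chemotherapy, day 4 only: "At the end of day 4, participants will no longer be required to consume the oral supplements". Leftover capsules are then counted to determine adherence.
- Hypothesis, item 4: the supplement will "Be adhered to (>80% consumption of supplements". Adherence is also a listed secondary outcome.

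**The concern.** The number of dosing days is part of the definition of the intervention. One sentence in the dispensing step gives a number that differs from the rest of the protocol and from the supply described in that same sentence. The phrase fixing the start on the day of chemotherapy closes off the charitable reading that the four days are only those after chemotherapy.

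The dispensing step is the point at which participants receive their capsules, written information and education, so it is a natural source for whoever drafts those instructions. It is repeated in each of three cycles. Adherence is determined from leftover capsules, so a participant who followed the 4-day wording exactly would return the same number as one who skipped a whole day of a 5-day course. The count alone could not tell them apart.

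**Working it through.** **Inputs.** 4 capsules per day (Ginger extract: "A regimen of 4 capsules per day will be selected"); 20 capsules per cycle (dispensing step); 4 days (dispensing step) or 5 days (abstract, overall study design, timeline); 3 cycles; adherence strictly above 80% (Hypothesis, item 4).

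**1. The plan's own supply figure.** Capsules = capsules per day × days = 4 × 5 = 20. The stated supply is reproduced with 5 days.

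**2. The day-by-day timeline.** Day of chemotherapy: 1 + 3 = 4. Days 1 to 4 after it: 4 × 4 = 16. Total 4 + 16 = 20 capsules over 5 days, which again matches the supply.

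**3. The 4-day wording.** Starting on the day of chemotherapy, four days are that day and post-chemotherapy days 1, 2 and 3. Capsules = 4 × 4 = 16, leaving 20 − 16 = 4 per cycle. Twenty capsules, 4 per day and 4 days cannot all be true.

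**4. Adherence under each reading.** Adherence = capsules taken / denominator. The protocol does not state the denominator, so both candidates are shown.

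| Course followed | Taken per cycle | Denominator 20 (dispensed) | Denominator 16 (4-day course) |
|---|---|---|---|
| 4-day wording | 16 | 16/20 = 80.0%, not above 80% | 16/16 = 100% |
| 5-day schedule | 20 | 20/20 = 100% | 20/16 = 125%, not meaningful |

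Over three cycles with the dispensed denominator, the 4-day wording gives 48/60 = 80.0%. Exceeding 80% takes at least 17 of 20 capsules in a cycle (85%), or 49 of 60 overall (81.7%).

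**5. Range of exposure affected.** Worst case: the 4-day wording is followed in every cycle. That is 1 day × 3 cycles = 3 of 15 days (20%), or 3 × 4 = 12 of 60 capsules, relative to the 5-day schedule. Best case: the participant instructions follow the day-by-day timeline, and 0 of 15 days are affected.

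**The case against.** The strongest reply is that this is one stray number in a document that otherwise agrees with itself. The same sentence gives a 5-day supply, the same section lists five adherence forms, and the timeline gives each of the five days its own dosing instruction. Staff and participants would have 20 capsules and five forms in front of them, and most would follow those. The participants' written information is not shown, and nothing says it repeats the 4-day phrase. This stands, and it limits the likely harm. It does not make the sentence consistent.

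A reader might infer stronger consequences that the documents do not support:

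- **That adherence is bound to fail.** This needs the 20 dispensed capsules as denominator, which is plausible given the count of leftovers but is not stated. It also needs the 80% figure to act as a pass mark for each participant, whereas it appears in a trial-level hypothesis.
- **That participants might take all 20 capsules in four days, and so a higher daily amount.** The same sentence fixes 4 capsules per day, and the abstract, the Ginger extract section and the timeline repeat it.
- **That day 4 outcomes would reflect an untreated period.** The nausea inventory is completed at the same time each day and covers the preceding 24 hours, so the day 4 form reaches back into day 3, a dosing day even on the 4-day wording. The FLIE uses a 5-day recall, most of which would also cover dosing days.
- **That mixed readings dilute the treatment contrast.** This is possible, but it depends on instructions that are not shown and cannot be sized from the protocol.

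**Conclusion.** The contradiction is real, and no reading of the sentence removes it: the dispensing step says 4 days where its own supply, its own list of forms, the abstract, the overall design and the timeline say 5. It is minor to moderate in weight. It concerns treatment duration at an operative step, but it is confined to one sentence.

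Its size is 4 of 20 capsules per cycle for anyone who follows the 4-day wording, and between 0 and 3 of 15 dosing days over three cycles. The adherence consequence is conditional: exactly 80.0%, just missing the criterion, if capsules dispensed are the denominator and the criterion is applied to individuals; 100% if the denominator is 16. This review takes no position on which duration is clinically right.

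**What to change.** Reconcile the sentence in the section on 7 days prior to chemotherapy with the abstract, the overall study design, the timeline and the capsule count, so that one number of dosing days appears throughout. Check that the participants' written information and verbal education give that same number. State the adherence denominator as the capsule count that follows from it, and say whether the 80% criterion applies per cycle or over all three cycles, and to individuals or to the group. If anyone has already been instructed from the 4-day wording, record which instruction they received so that their capsule counts can be interpreted.

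The cost is one protocol correction and a check of the participant materials. No extra patients or outcome measurements are needed, and the sample size is unaffected.

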### Pre chemotherapy – 1 day prior to chemotherapy

The following tools will be completed by the participant 24 hours before chemotherapy:

• One FACT-G/FACIT-F questionnaire

• One ESAS questionnaire

### Day of chemotherapy

The following tools will be completed by the participant on the day of chemotherapy:

• One INVR questionnaire will be completed before chemotherapy commences.

• One CINV susceptibility questionnaire will be completed any time after chemotherapy has commenced.

• One adherence questionnaire.

Additionally, the participant is to consume one ginger/placebo capsule 1 hour before the administration of chemotherapy and then once every 4 hours after that for the remaining 3 capsules. The timing will be discussed with the participant to help ensure the participant understands the regimen.

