### Predisposing factors influence individual susceptibility to chemotherapy-induced nausea and vomiting

Multiple factors are reported to influence the individual risk of a patient developing CINV [31]. These factors relate not only to the treatment protocol but also the patient’s lifestyle, mental state, and previous experience with nausea and vomiting in other settings [32-34]. Consequently, while the emetogenicity of the treatment protocol is the major determinant of CINV risk, a patient with multiple predisposing factors can experience significant levels of CINV despite being prescribed a low emetogenic chemotherapy regimen. Of particular concern is the development of anticipatory nausea and vomiting, a conditioned response that is difficult to treat, and the gradual resistance to anti-emetic therapy after multiple chemotherapy cycles [35].

These factors represent a significant set of potential confounding variables for RCTs in this setting. To date, all trials in this area have recruited patients that have already experienced nausea and vomiting in previous chemotherapy cycles. This allows for the potential recruitment of patients with an already established resistance to additional anti-emetic therapies. Furthermore, if lifestyle factors such as alcohol intake and previous experience of motion sickness, which have been shown to influence CINV risk, are not screened for, this may result in a study comprised of two groups with a predisposed heterogeneous response to CINV. To date, this has not been thoroughly controlled for and therefore, may account for some of the difference in the results between previous trials. We have developed a short questionnaire that aims to assess these factors and will be the first study to factor this into our post-study statistical analysis.

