### Secondary outcomes

• The frequency and severity of acute and delayed vomiting

• The frequency and severity of acute and delayed retching

• Change in ratings of cancer-related fatigue

• Adequacy of supplement blinding

• Change in nutrition status

• Incidence and severity of symptoms associated with treatment

• Change in quality of life

• Change in quality of life caused by nausea and vomiting

• Patient adherence to intervention

• Influence of previously identified factors that affect the generation of CINV

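### The questionnaire on predisposition to nausea is completed after treatment starts, so analyses that use it can be biased, probably modestly; completing it once before randomisation avoids this

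*Protocol article*

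**What the plan says.** The section on the CINV susceptibility questionnaire says the form was "developed for use in this trial to determine participants’ predisposition to CINV". Its examples are alcohol intake, "previous experience of nausea and/or vomiting from causes other than chemotherapy" (motion sickness and pregnancy are named), age and gender. The Background section on predisposing factors treats such factors as potential confounders and says this trial "will be the first study to factor this into our post-study statistical analysis". The secondary outcomes include "Influence of previously identified factors that affect the generation of CINV".

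The Timeline fixes the order of events:

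- About 7 days before chemotherapy, after consent: "Participants will be randomised and provided with a 5 day" supply of capsules. The booklet is handed over at the same consultation.
- On the day of chemotherapy: "the participant is to consume one ginger/placebo capsule 1 hour before the administration of chemotherapy".
- Later that day: "One CINV susceptibility questionnaire will be completed any time after chemotherapy has commenced".

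No section schedules an earlier completion. The booklet for a cycle holds one susceptibility form, and the Timeline is to be repeated for three cycles, so as written the form is completed up to three times.

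**The concern.** A covariate is safe to adjust for when treatment cannot have affected it. This one is self-reported on a day when acute nausea may already be present, and nausea is what ginger is meant to change. If a nauseated person recalls more past motion sickness or pregnancy sickness, the reported value carries part of the treatment effect, and adjusting for it takes that part away. Whether the form is completed at all may also depend on how the participant feels. Blinding does not block this route, because it runs through the symptom and not through knowledge of allocation. Stratification by emetogenicity concerns a different variable.

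At stake are any covariate-adjusted treatment effects and the secondary outcome on prognostic factors. The article presents control of these factors as an advance on earlier trials. No analysis plan can turn a measurement taken after treatment into one taken before it.

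**Working it through.** **Order of events.** Randomisation (about 7 days before), then the first capsule (1 hour before), then the start of chemotherapy, then the questionnaire (any time after). The form follows all three.

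**The plan's own figure.** The only design figure is 73 per arm. It cannot be reproduced, because the article gives no mean difference, SD or rates. Solving backwards for 80% power and two-sided alpha 0.05 gives a standardised difference of (1.960 + 0.842) × √(2/73) = 0.464, or 0.467 with the t distribution. I use 0.46 only to set a scale; the percentages below do not depend on it.

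**Model (all inputs are assumptions).** True susceptibility X has SD 1 and correlates 0.3 with the nausea outcome Y, whose SD is 1 within arms. The treatment effect on Y is τ = −0.46. Early nausea A, present when the form is completed, has SD 1 within arms and correlates r = 0.5 or 0.8 with Y. A fraction f of τ has already acted on A. The reported score is S = X + gA + noise (SD 0.5), where g is the shift in reported susceptibility per SD of early nausea.

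**Formula.**

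- Difference between arms in S: g·f·τ
- Within-arm slope of Y on S: β = (0.3 + g·r) / (1.25 + g² + 0.6·g·r)
- Adjusted effect: τ − β·g·f·τ, so the proportion lost is f·g·β

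Example with g = 0.2, r = 0.5, f = 1: 0.2 × 0.40 / 1.35 = 0.059, and the adjusted effect is −0.46 × 0.941 = −0.433.

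| g | f = 0 | f = 0.5 (r = 0.5 to 0.8) | f = 1 (r = 0.5 to 0.8) |
|---|---|---|---|
| 0 | 0% | 0% | 0% |
| 0.1 | 0% | 1.4 to 1.5% | 2.7 to 2.9% |
| 0.2 | 0% | 3.0 to 3.3% | 5.9 to 6.6% |
| 0.3 | 0% | 4.7 to 5.5% | 9.4 to 10.9% |
| 0.5 | 0% | 8.3 to 10.1% | 16.7 to 20.1% |

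A simulation with 1,000,000 subjects and f = 1 agrees to within about 0.1 percentage point. Without the noise term the largest entry becomes 0.5 × 0.70 / 1.49 = 23%.

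**The secondary outcome.** The same slope β describes how strongly reported susceptibility appears to predict nausea. It is 0.3/1.25 = 0.24 when g = 0. At g = 0.1 it is 0.35/1.29 = 0.27 (r = 0.5) to 0.38/1.308 = 0.29 (r = 0.8), and at g = 0.3 it is 0.45/1.43 = 0.31 to 0.54/1.484 = 0.36. So the association would be overstated, and this does not require ginger to have acted yet.

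**Missing forms.** The article gives nothing from which to size this, and its direction is open.

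**The case against.** The strongest reply is that the listed items are mostly history or fixed traits. Treatment cannot change age, gender or past motion sickness, so bias needs nausea on the day to distort recall or completion, and nothing in the article shows that it does. This stands, and it is why the small values of g are the more plausible ones.

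Timing also limits the size. In cycle 1 the form is due on the day of chemotherapy, when only one capsule must have been taken and most delayed nausea has not yet occurred. A reader might let the whole outcome shift the answers. With S = X + bY and no noise, the proportion lost is b(0.3 + b)/(1 + 0.6b + b²), or 9%, 14% and 26% for b = 0.2, 0.3 and 0.5. The schedule does not support that, because the cycle 1 form precedes most of the outcome.

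The Statistical analysis section names no covariate-adjusted primary model. Which items enter which model, and from which cycle, may be settled in a document not shown. That is fair, but it bears on how the answers are used and not on when they are collected.

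A reader might also infer that the repeat forms in cycles 2 and 3 add bias of their own. They do so only if later values are used, and no section says that they will be. Otherwise they are redundant.

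**Conclusion.** The timing weakness is real and is fixed in the text: a measure of predisposition intended for the analysis is taken after randomisation, after the first capsule and after chemotherapy has begun. Its consequence is conditional. If current nausea shifts the answers, an adjusted treatment effect can be attenuated by 0% to roughly 20% under the assumed inputs. The lower end is the more plausible, and the loss is zero if answers do not shift or if treatment has not yet acted on nausea when the form is completed. Under the same model, the association examined as a secondary outcome would be overstated.

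A reader might infer that the trial's main comparison is compromised, or that adjustment is bound to remove part of the effect. The article supports neither: the unadjusted randomised comparison does not use the form, and no evidence of shifting answers is given. This is a worthwhile correction to adjusted and secondary analyses, made mainly because it is nearly free and because such bias could not be verified or undone after data collection.

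**What to change.** Have the questionnaire completed once, at the consultation about 7 days before cycle 1, after consent and before randomisation; at the latest, before the first capsule. State that this single value is used in all adjusted analyses and in the secondary outcome on prognostic factors. Remove the form from the cycle 2 and 3 booklets.

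The cost is a minor amendment and about 5 extra minutes (the article's own estimate) at a consultation that already covers consent, instruction and the nutritional assessment. It is offset by one form fewer on the first day of chemotherapy and two fewer in later cycles.
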